### Economic Analysis

This will assess whether HIP represents a cost-effective use of scarce NHS resources when compared to TAU. In line with guidance by NICE[47], costs will be calculated from the perspective of the NHS and personal social services and encompass those costs that are potentially related to the intervention in question. Thus we will monitor the levels of resource use associated with completing the HIP (including those associated with any associated tests/investigations that are recommended, changes in medication use and any other service referrals). For patients in both arms we will also monitor visits to other health care professionals, any admissions to hospital, and medication usage. Appropriate unit costs will subsequently be assigned to each of these items e.g. [46].

The measures of effectiveness employed in the economic analysis will be the 5 dimensions of the EQ-5D[48], used to calculate quality-adjusted-life-years (QALYs) associated with both the intervention and TAU.

An economic model will be constructed to estimate both the mean overall cost and mean overall effect associated with both the intervention and treatment as usual. If one of these options were shown to be less costly and more effective than the other then this would suggest that it 'dominates' the other, and represents a cost-effective use of scarce resources. Alternatively, the incremental cost-effectiveness ratio associated with the HIP will be estimated and assessed in relation to a set of cost-effectiveness thresholds e.g. a threshold of £20,000-£30,000 per QALY is recommended by NICE[47]. The associated level of uncertainty will also be characterised e.g. by estimating the cost-effectiveness acceptability curve [CEAC] for each intervention[49]. Additionally, sensitivity analysis will be undertaken to assess the robustness of conclusions to key assumptions.

### Cardiovascular risk

95% confidence intervals will be calculated for change in QRISK^©^2 for the HIP group participants.

### Process observation

Data from the HIP Audit Forms will be analysed using SPSS. Patient semi-structured interviews will be recorded by taking notes in the interview and seeking feedback from the patient participant that the notes accurately reflect what was said. The nurse focus groups and doctors' telephone interviews will be audio-recorded and transcribed verbatim. Transcripts from all interviews and focus groups will be coded using thematic analysis[50]. The results will then be returned to the participants for member checking[51].

### Potential Bias

The subjective nature of the self-report instruments, used for assessment, is accepted and every effort will be made to minimise potential bias which may occur due to this dynamic. In particular, patients may over or under report their health status depending on the trial arm to which they have been assigned. We acknowledge there may be attrition so to enable an evaluation of the effects of this on the primary outcome we will undertake a secondary per protocol[PP] analysis to compare with the ITT.

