### Number of Participants

#### Part 1

A sample size of 50 MHNs will be sought (25 in the HIP and 25 in the TAU group), with 5 patients each resulting in an overall sample size of 250 patients (125 in the HIP and 125 in the TAU group). Based on a standard deviation of about 12 points as found in MOS patients (adults in various settings with SMI in the US), a difference in means between intervention and TAU of 6 points in the SF36v2 PCS subscale is equivalent to a medium effect size. The proposed sample size gives a power of 86% to detect this if an intraclass correlation of 0.1 is assumed and nearly 80% if an intraclass correlation of 0.2 is assumed using a 2-sided significance level of 0.05 and allowing for an estimated 20% attrition rate i.e. 1 patient per nurse.

All MHNs in the HIP and TAU groups will be invited to participate in the online PHASe adapted at baseline and one year. Response rates will be reported. All patients remaining the HIP Group at one year will provide data for evaluation of any change in their QRISK^®^2 Scores. Retention rates will be reported.

#### Part 2

The patient records of the 36 randomly selected patients from the HIP Programme Group will be audited using the HIP Audit Form. We will purposefully recruit from the HIP Group (on completion of Part 1) 10 patients to participate in the Patient Semi-structured Interviews, 10 nurses to participate in a Focus Group (per Trust study site) 5 psychiatrists and 5 GPs to participate in the telephone interviews. (30 in total). The aim of this element of the project is to elicit general feedback that will help in refining and further developing the HIP. The qualitative literature indicates that this number of data collection interviews per homogenous professional or patient group should allow us to reach saturation of themes [46].

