### Inclusion in Analysis

An intention to treat (ITT) analysis will be performed. The ITT analysis set will comprise all patients who were randomised to a group at baseline (HIP Programme or TAU group), irrespective of any change to the other group over the course of the trial. This is the main analysis and will be used for evaluation of all endpoints. However, we acknowledge there may be attrition due to nurses leaving teams and where patients may be unavoidably switched to a nurse participant caseload in a group other than the one they were randomised to at baseline or to a MHN not in the study. To enable an evaluation of the effects of this on the primary outcome we will undertake and report a secondary per protocol [PP] analysis. HIP and non-HIP patients will be included in groups on an intention to treat basis. The primary analysis will include non-missing data only. However, where there is attrition at follow up the baseline characteristics of missing and non-missing values will be compared. Further, we will perform sensitivity analyses by (i) assuming zero change in scores and (ii) employing current multiple imputation techniques.

A per protocol analysis will also be performed. Per protocol will be defined as the participant remaining in the same arm of the study as at randomisation.

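### Comparing the per-protocol and ITT results cannot show the effect of attrition, and zero change is a weak substitute for a check on outcomes missing not at random

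*Protocol article*

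**What the plan says.** Four statements in the protocol article bear on this point.

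- Potential Bias: "We acknowledge there may be attrition so to enable an evaluation of the effects of this on the primary outcome we will undertake" a secondary PP analysis, to be compared with the ITT.
- Inclusion in Analysis, on the data used: "The primary analysis will include non-missing data only".
- Inclusion in Analysis, on the PP set: "Per protocol will be defined as the participant remaining in the same arm of the study as at randomisation". The PP analysis is introduced there for nurses leaving their teams and for patients who move to the caseload of a nurse in the other arm or outside the study.
- Inclusion in Analysis, on missing follow-up: patients with and without a follow-up value are compared at baseline. Then: "Further, we will perform sensitivity analyses by (i) assuming zero change in scores", with multiple imputation as the second sensitivity analysis.

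The word attrition also appears under Number of Participants, where the power is computed "allowing for an estimated 20% attrition rate i.e. 1 patient per nurse". There it means patients who do not contribute to the analysis.

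**The concern.** Potential Bias gives the PP analysis the job of showing what attrition does to the primary outcome, without limiting attrition to caseload moves. A reader coming from the sample-size section would take it to mean lost outcomes. But the ITT estimate is itself based on completers, and the PP estimate is based on a subset of those completers. Any bias from selective loss is common to both, so close agreement could be taken as reassurance that it does not give.

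That puts the weight on the two sensitivity analyses for missing data. Standard multiple imputation assumes that loss depends only on what was observed. The other analysis, zero change, does depart from that assumption, but in one fixed way that is hard to defend as a model of patients who leave a 12-month study. What is at stake is whether the trial can say how far its primary result depends on the patients it did not see again.

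**Working it through.** **Inputs from the document** (Number of Participants): 25 nurses per arm; 5 patients per nurse, 125 per arm; 4 per nurse after 20% attrition, so 100 per arm; SD 12; difference 6 points; two-sided 0.05; ICC 0.1 or 0.2.

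**Step 1. The plan's own figure.** Design effect = 1 + (4 − 1) × ICC.
- ICC 0.1: 1.3; effective n = 100/1.3 = 76.9 per arm; power 87.3% (normal), 86.0% (t, 48 df). Stated: 86%.
- ICC 0.2: 1.6; effective n = 100/1.6 = 62.5; power 79.8% (normal), 78.2% (t, 48 df). Stated: nearly 80%.

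The power reproduces and is not in dispute. It also confirms that attrition in that section means patients lost from the analysis.

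**Step 2. What the ITT/PP difference contains.** Let S be the patients with a 52-week score. The ITT estimate uses S. I assume that PP uses the same observed scores, since no other handling is stated; it then uses the members of S who did not change arm. Within an arm,

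PP mean − ITT mean = (share of switchers in S) × (mean of stayers in S − mean of switchers in S).

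No lost patient's score enters this expression. With no switching the share is 0 and the two estimates are identical, however many patients are lost and for whatever reason.

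**Step 3. Size, by illustration.** Assumptions, not document figures: ICC 0.1; 20% lost in each arm, at random in TAU; in HIP, 36% lost below the arm median and 4% above it, so nine in ten of those lost are low scorers. Mean differences over 4,000 simulated trials:

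| True effect | Switching | All patients | Observed ITT | PP (same arm) |
|---|---|---|---|---|
| 0 | none | 0.0 | 1.9 | 1.9 |
| 6 | none | 6.0 | 7.9 | 7.9 |
| 6 | 10% | 4.8 | 6.7 | 7.9 |

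Hand check of the 1.9: for a normal score with SD 12, each half lies on average 12 × √(2/π) = 9.57 points from the centre. Among observed HIP patients the low half makes up 0.64/(0.64 + 0.96) = 0.4, so their mean is (0.6 − 0.4) × 9.57 = 1.9. The size depends on the assumed selection. If seven in ten of those lost were low scorers (28% lost below the median, 12% above), the low half would make up 0.72/(0.72 + 0.88) = 0.45 and the bias would be (0.55 − 0.45) × 9.57 = about 1.0. With no selection it is 0. At every strength, without switching, ITT and PP agree exactly.

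With 10% switching they differ by 7.9 − 6.7 = about 1.2. That matches the dilution from switching, 6 × (0.10 + 0.10) = 1.2, and says nothing about lost outcomes.

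**Step 4. Zero change.** Let t be the mean change in TAU, t + 6 in HIP, and p the fraction lost at random in each arm. Setting lost patients to zero change gives

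(1 − p)(t + 6) − (1 − p)t = 6(1 − p).

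At p = 0.20 this is 4.8, whatever t is; at p = 0.10 it is 5.4 and at p = 0.30 it is 4.2. A separate simulation with 20% lost at random gave 4.79. If loss differs by arm, the result is 6(1 − pHIP) − t(pHIP − pTAU), so it then also depends on the trend and need not be conservative. In all cases 250 scores are entered where about 250 × 0.8 = 200 were measured.

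**Step 5. What a delta adjustment would show.** If imputed scores are lowered by dHIP points in HIP and dTAU in TAU, at 20% loss the estimate moves by −0.2 × dHIP + 0.2 × dTAU. A 6-point shift in HIP alone moves it by 0.2 × 6 = 1.2 points. Reported over a range of shifts, this tells a reader how different the lost patients would have to be before the conclusion changes.

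**The case against.** The best reply is that Potential Bias is a shortened repeat of Inclusion in Analysis. There, attrition in this connection means nurse turnover and patients changing caseload, and a same-arm PP set can speak to arm switching, as the third row of the table shows. For missing scores the same section plans a baseline comparison, zero change and multiple imputation. This stands: attrition does not rest on the PP analysis alone. It does not rescue the Potential Bias sentence, which has no such limit, while the sample-size section and the missing-data sentence use the same word for lost outcomes.

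A reader might infer that the ITT/PP comparison is bound to mislead. The document does not support that: ITT is the main analysis, PP is secondary, and other missing-data analyses are planned.

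A reader might also infer that the PP set is wrong because it keeps HIP patients whose nurse never completed a HIP with them. The rule indeed does not measure receipt, but the protocol never says that it does. Keeping only patients with a completed HIP would compare engaged HIP patients with all TAU patients, a further selection after randomisation. That is a debatable choice, not a correction.

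Finally, zero change is only a sensitivity analysis, its shrinkage is known arithmetic, and imputation details usually sit in the SAP, which is not shown. All true. But zero change is fixed here by name, and the current imputation techniques mentioned beside it are not said to depart from missing at random.

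**Conclusion.** The point holds in a limited form. As written in Potential Bias, the PP-versus-ITT comparison cannot do the job it is given: patients without a 52-week score are in neither set. This is structural and needs only that both analyses use observed scores. The bias of about 1.9 points (about 1.0 under weaker selection) is an illustration resting on assumed selective loss in one arm; the document gives no figure for this.

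Zero change turns 6 points into 4.8 at the planned 20% attrition, given equal loss at random, and treats imputed scores as data. Read with standard multiple imputation, it leaves no sound check on outcomes missing not at random.

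Neither the sample size nor the primary analysis is affected. The consequence is one of interpretation: agreement between ITT and PP may be misread as robustness to attrition. A smaller gap is that the PP definition does not say where a patient moved to a nurse outside the study belongs, although the section itself raises that case.

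**What to change.** 1. In Potential Bias, remove the attrition role of the PP analysis and refer to the missing-data analyses under Inclusion in Analysis.
2. State that the PP analysis addresses the effect of arm switching only, and state before the data are seen how patients moved to a non-study nurse are classified in each arm.
3. Assess lost outcomes with the multiple imputation already planned, using an imputation model that allows for nurse clusters.
4. Replace zero change with delta-adjusted multiple imputation: shift the imputed 52-week PCS over a stated range, separately by arm, and report the estimate and confidence interval across the range. The range itself can be set in the SAP.

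The cost is a few sentences and a little more analysis work. No new data are needed, and the main analysis and sample size are unchanged.

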## Discussion

Physical comorbidities are common in people with SMI and have a profound effect on both quality and length of life. Poor physical health compounds the already major issue of social exclusion in this population. Preventing, recognising and treating physical comorbidity is central to holistic care and this is reflected in standards and guidelines from the Department of Health, the Nursing and Midwifery Council and the National Institute of Health and Clinical Excellence. Despite recent policy drivers to improve screening and intervention, concerns remain about the confidence and competence of the existing workforce to address this problem. Two studies, five years apart, highlighting this deficit in the MHN workforce in the UK have used observational designs in small convenience samples[26,52].

To date the only published experimental studies of implementation of a package of interventions to improve physical health in SMI have included a number of service evaluations and one RCT that aimed to improve screening rates [32,53-55]. With the exception of the HIP case series evaluation [32], these studies introduced new staff in a physical health role as an adjunct to the usual care delivered by the mental health team for the duration of a specific pilot project [53-55]. There remains a need to find a cost-effective evidence-based solution that avoids expensive and lengthy retraining or restructuring of services and roles and enables physical health screening and intervention on a population level.

In designing the HIP Programme, our focus has been to enable any MHN in contact with the person with SMI, to exploit the opportunity to monitor physical health and offer appropriate evidence-based or recommended intervention through their usual contact and role, rather than as an adjunct service. This is a pragmatic approach to the problem, yet it remains complex in terms of its evaluation and dissemination. Complex interventions contain several interacting components[56]. The HIP Programme targets the MHN, the patient and the organisation and requires them all to interact. For example, a MHN using the HIP with a patient will need to find time within their existing role to engage the patient in the HIP process and communicate within their own organisation and across the primary-secondary care interface to enable additional screening or access to intervention for the patient.

The Medical Research Council recommend researchers pay attention to the interplay between development, feasibility, evaluation and implementation when designing complex health interventions[56]. In the development stage, initial piloting of the HIP was positive with mental health nurses, patients, psychiatrists and GPs reporting that it is acceptable, avoids duplication of work, enables previously unidentified physical comorbidities to be uncovered and improves care planning and interface communication. Clinical utility and acceptability were then established in an exploratory case series within a community MH service in Scotland[32].

To maximise success in the future implementation of the HIP we have included an education package to meet the individual and organisational needs of the staff most likely to be in contact with people with SMI. The cluster design with the MHN as the cluster has been adopted because the focus of the intervention depends on the training and adoption of the HIP by MHNs. In evaluating the success of our intervention, the HIP and the training package together [the HIP Programme], we will evaluate patient outcomes and conduct a process observation. This will allow us to report education outcomes (any change in nurse knowledge of and attitudes towards a physical healthcare role using the adapted PHASe [40]) in addition to our primary evaluation of effectiveness and cost effectiveness.

The primary end point of this proposed study, change in physical related quality of life, has meaning to patients, carers, practitioners and policy makers and will formally explore the clinical potential of the tool. We have a specific qualitative element to explore patient, practitioner and medical experience of the HIP. Qualitative and audit data will enable us to more fully test the acceptability of this approach and further refine it as necessary. The health economic element of the study will provide important information about the costs of disseminating this approach across the NHS in terms of any additional service costs and Quality Adjusted Life Years (QALYs). The evaluation of HIP trainees knowledge and attitude towards physical health post HIP training will inform future workforce training and implementation plans.

If successful, this study will demonstrate the clinical and economic potential of an innovative brief training package and pragmatic clinical profile (the HIP Programme) that makes use of and builds upon the existing skills of MHNs who have the most contact with these patients and who already coordinate care and treatment between services. MHNs working in the community will be trained to profile and plan care around individual physical health issues in a real world setting. If successful, the quality of our evidence will inform regional dissemination and a future definitive effectiveness study to enable policy makers to recommend the HIP Programme across the NHS.

## Current Study Status

NHS ethics approval was granted in December 2010 and Research and Development Approval from the sponsor NHS Trust site in March 2011. Active recruitment commenced on 04 April 2011.

## List of abbreviations

CONSORT: Consolidated Standards of Reporting Trials; COPD: Chronic Obstructive Airways Disease; CRTU: Clinical Research Trials Unit; CVD: Cardiovascular Disease; DH: Department of Health; EQ-5D: EuroQuol Dimension Questionnaire; GP: General Practitioner; HIP: Serious Mental Illness Health Improvement Profile; HRU: Health Resource Use; ITT: Intention to Treat; MCQ: Multiple Choice Questionnaire; MCS: Mental Component Summary Score; MH: Mental Health; MHN: Mental Health Nurse; MHRN: Mental Health Research Network; MOS: Medical Outcome Study (see SF-36v2); NHS: National Health Service; NICE: National Institute of Health and Clinical Excellence; PHASe: Mental Health Nurse Physical Health Attitude Scale.
